#### Mechanism exploration

2.7.4

##### Proteomic analysis

2.7.4.1

A quantitative proteomics analysis will be performed based on a 4D-DIA method. The samples were mixed with 1%SDC/100 mM Tris-HCL/10 mM TCEP/40 mM CAA (pH = 8.5) and incubated for 1 h at 60°C for one-step reduction and alkylation. LC–MS/MS data acquisition was carried out on a Q Exactive Plus mass spectrometer coupled with an Easy-nLC 1,200 system. The raw MS data were processed by DIA-NN software (V1.7.16) using the library free method. The general function databases that provide annotations (GO, KEGG, etc.) are used to annotate the identified proteins to understand the functional characteristics of different proteins. Data will be filtered by half the number of actual values in either group and conducted logarithmic transformation and imputation with the random value method. The filled data will be used for subsequent analysis.

##### Protein validation

2.7.4.2

ELISA kits will be applied to detect differences in the DEP levels of serum in patients in the acupuncture group and the control group before and after treatment. Samples will be diluted appropriately, and the data will be analyzed in duplicate according to the manufacturer’s instructions.

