**Methods:**

A total of 132 patients involving four hospitals will be randomized at a 1:1:1 ratio in the acupuncture group, control group, and sham acupuncture group. All the patients will receive basic treatment, and the patients in the acupuncture and sham acupuncture groups will also receive either acupuncture or sham acupuncture treatment, respectively, at six sessions each week for a 2 weeks period, followed by 3 months of follow-up. The primary outcome will be the change in the National Institute of Health Stroke Scale (NIHSS) scores after treatment. The secondary outcomes will include the Fugl-Meyer Assessment (FMA) scale scores and the Barthel Index (BI). Adverse events that occur during the trial will be documented. To discover differentially expressed proteins (DEPs) and their roles between the ACI subjects and healthy controls, we will also perform 4D-DIA quantitative proteomics analysis, and the DEPs will be confirmed by enzyme-linked immunosorbent assay (ELISA). This study was approved by the institutional review board of the First Teaching Hospital of Tianjin University of Traditional Chinese Medicine (TYLL2023043). Written informed consent from patients is required. This trial is registered in the Chinese Clinical Trial Registry (ChiCTR2300079204). Trial results will be published in a peer-reviewed academic journal.

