### Participant recruitment

2.2

The eligible consecutive participants will be enrolled in the First Teaching Hospital of Tianjin University of Traditional Chinese Medicine, Tianjin Huanhu Hospital, First Hospital of Jilin University, and Huzhou Central Hospital. This trial will include an enrollment and allocation period of 6 days every week over a 2 weeks intervention period followed by a 3 months follow-up period. The gender- and age-matched healthy people will also be enrolled as the health group that will be analyzed by proteomic analysis investigations. We will obtain the informed consent from each participant or an appointed legal representative if the participant lacks the decision-making capacity. The flowchart of the study is shown in Figure 1, and the mechanism exploration procedure is shown in Figure 2.

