**Figure 2 fig2:**
[figure not shown]
Study design and workflow. AG, acupuncture group; HG, health group; DDA, data-dependent acquisition; DIA, data-independent acquisition.

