### Sample collection and classification

2.5

The peripheral blood will be collected in the morning. Blood samples will be taken from the acupuncture and the control groups before and after treatment; then, the participants from both groups will be asked to wait for 30 min after the blood clotted at room temperature; serum will be collected after centrifuging at 3,000 g for 10 min at 4°C and will be stored at −80°C for proteomic analysis and ELISA validation. In total, 10 blood samples will also be taken from 10 gender- and age-matched healthy people for proteomic analysis.

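### The abstract promises ELISA confirmation of proteins that differ between stroke patients and healthy people, but the ELISA as described has no healthy serum and can only test change or treatment response within patients

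*Protocol article*

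**What the plan says.** All places are in the Protocol article.

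- **Abstract, Methods**, on what the proteomics is for: "To discover differentially expressed proteins (DEPs) and their roles between the ACI subjects and healthy controls". The same sentence adds: "the DEPs will be confirmed by enzyme-linked immunosorbent assay (ELISA".
- **Section 2.2, Participant recruitment**: matched healthy people are "enrolled as the health group that will be analyzed by proteomic analysis investigations".
- **Section 2.5, Sample collection and classification**: serum from the acupuncture and control groups "will be stored at −80°C for proteomic analysis and ELISA validation". The healthy samples are described separately: "10 blood samples will also be taken from 10 gender- and age-matched healthy people for proteomic analysis".
- **Section 2.7.4.2, Protein validation**: "ELISA kits will be applied to detect differences in the DEP levels of serum in patients in the acupuncture group and the control group". The sampling is pre- and post-treatment.
- **Figure 2 legend**: the only groups abbreviated are "AG, acupuncture group; HG, health group".
- **Introduction, last paragraph**: the initial set of DEPs is introduced with reference to expression changes that acupuncture might cause, and is then to be confirmed by ELISA.
- **Section 3, Discussion**: the proteomics is to clarify how acupuncture works, and the DEPs are then verified by ELISA.

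**The concern.** A verification assay has to re-measure the difference that it is meant to verify. The abstract's difference is between patients and healthy people. The ELISA compares two randomised patient arms before and after treatment, and no section places healthy serum in it.

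A protein can differ between stroke and health and yet not respond to acupuncture, and the reverse is also possible. A null ELISA result between the arms would therefore not refute a disease DEP, and a positive one would not confirm it. If the study is reported in the abstract's words, readers would take a patient-versus-healthy finding as checked by a second method, when it would rest on mass spectrometry with 10 healthy people. The ELISA would also be unable to show whether a change after treatment moves towards or away from the healthy level.

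**Working it through.** The plan gives no figure for this point, so there is none to reproduce. The check compares the contrasts, then sizes the remedy.

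**1. Which groups enter which assay, as stated**

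| Samples | Proteomics | ELISA | Source |
|---|---|---|---|
| Acupuncture group, before and after | yes | yes | 2.5, 2.7.4.2 |
| Control group (randomised, no acupuncture), before and after | yes | yes | 2.5, 2.7.4.2 |
| Healthy people, 10 samples | yes | not stated | 2.2, 2.5 |

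The control group in section 2.7.4.2 cannot be read as the healthy controls. The sentence speaks of patients measured before and after treatment, and section 2.3 defines the control group as a randomised arm.

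**2. What the ELISA can estimate**

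For one protein, write the ELISA means as A0 and A1 (acupuncture, before and after), C0 and C1 (control, before and after) and H (healthy).

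- Treatment response: T = (A1 − A0) − (C1 − C0). All four terms are available.
- Change over time: A1 − A0 or C1 − C0. Available.
- Disease contrast, with equal arms: D = (A0 + C0)/2 − H. H is not available.

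No combination of A0, A1, C0 and C1 gives H, so D cannot be obtained from the stated ELISA. T does not contain H, so T being zero or non-zero says nothing about D.

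**3. Which contrast defines the DEPs**

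- ACI versus healthy: the abstract. The Figure 2 legend is consistent with this.
- Acupuncture-related change: the Introduction's last paragraph and the purpose stated in section 3.

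The ELISA in section 2.7.4.2 matches the second definition and not the first.

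**4. Size of the remedy, in wells per protein**

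Inputs: 10 healthy samples (2.5), assays in duplicate (2.7.4.2), two patient arms and two time points (2.5, 2.7.4.2), 44 per arm, or 36 before the allowance for loss (2.4). The number of patients assayed is not stated, so a range is shown.

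- Healthy sera: 10 × 2 = 20 wells.
- All 44 per arm, no loss: 44 × 2 × 2 × 2 = 352; 20/352 = 5.7%.
- 36 per arm with both samples: 36 × 2 × 2 × 2 = 288; 20/288 = 6.9%.
- 10 per arm (an assumption, for illustration): 10 × 2 × 2 × 2 = 80; 20/80 = 25%.

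The absolute addition is 20 wells in every case.

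**The case against.** The strongest reply is that the abstract's wording is loose and the main text means something else. The Introduction and section 3 connect the DEPs with the effect of acupuncture. Section 2.5 sends before-and-after serum from both arms to proteomics, so treatment-related DEPs could be found there, and for those the planned ELISA is the right comparison. Testing whether disease-associated proteins respond to acupuncture is also a coherent mechanism step. Diagnostic biomarkers appear in the background discussion rather than in the stated purpose.

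Much of this stands. It means that the document does not settle the discovery contrast, and that the ELISA is not useless. It does not make the abstract and section 2.7.4.2 agree: the only place that names the two groups being compared names patients and healthy controls, and promises confirmation of the result.

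A second reply is that an article condenses the full protocol, and that Figure 2 was not visible here beyond its legend. Either could allocate sera to assays. This lowers certainty about what will happen in the laboratory. It does not remove the conflict, because the article is not silent: it names the ELISA groups and gives the two sample sets different uses.

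Three stronger readings are tempting and are not supported:

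- *Healthy serum will certainly never be assayed by ELISA.* The text assigns it to proteomics only. Its absence from the ELISA is an inference from that, not a stated exclusion.
- *Nothing can be said about patients versus healthy people.* The mass spectrometry still measures that difference and might show the direction of change; what is lacking is the second method.
- *Adding the healthy sera would confirm the DEPs.* Re-assaying the 10 samples used for discovery checks the measurement platform. It is not replication in new people.

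**Conclusion.** The point holds as a conflict between stated parts of the article. Followed as written, the ELISA can test treatment response or change over time within patients, but cannot verify an ACI-versus-healthy difference, which is what the abstract says it will confirm. The discovery contrast is also described in two ways.

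The conclusion takes sections 2.2, 2.5 and 2.7.4.2 at their word on which sera go to which assay. It depends on no power or sample-size assumption. The reach is limited to the exploratory mechanism aim. A reader might infer that the trial's efficacy result is weakened, but the NIHSS comparison uses none of these assays. The change is worth making because it is cheap and determines what the mechanism component may claim.

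**What to change.** State in section 2.7.4.1 which contrast defines the DEPs, and use the same definition in the abstract and the Introduction. Then take one of two routes.

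- **If the DEPs are defined by ACI versus healthy:** in section 2.5, assign the 10 healthy sera to ELISA as well as proteomics. In section 2.7.4.2, run them in duplicate alongside the patient sera, on the same plates and kit lots. Report two results per protein separately: patients at baseline versus healthy, labelled as technical verification in the same samples, and acupuncture versus control change, labelled as treatment response.
- **Otherwise:** describe the ELISA as a treatment-response test and remove the claim that it confirms the disease contrast. This needs only rewording.

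The first route costs 20 wells per protein and needs no new participants or visits. It requires no further blood draw provided enough healthy serum is kept; the article gives no volumes, so this must be checked. The decision should be made before proteomics uses up the healthy serum. State the number of patients to be assayed at the same time, since the relative cost depends on it.

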### Statistical analyses

2.8

Quantitative variables will be presented with mean ± SD. The Shapiro–Wilk test and box plots will be used to assess the homogeneity of the quantitative variables. All continuous and independent variables in the groups will be performed by Student’s *t*-test at baseline. The Mann–Whitney U test will be selected if the variance was not homogeneous between two groups. Stata software will be used to analyze the data according to the intention-to-treat principle, and a two-sided *p*-value less than 0.05 was considered significant.

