### Estimation of sample size

2.4

In this study, we aim to compare the difference in the NIHSS score between the acupuncture group and sham acupuncture group after the treatment. Sample size calculations were performed for a simple comparison of the two groups. According to a previous study (Sun and Wu, 2019), the NIHSS scores of mean ± SD between the two groups were 6.2 ± 2.1 and 4.9 ± 1.8, respectively, after the treatment. A total of 36 participants per treatment group (108 in total) were required when setting a one-sided test with *α* = 0.025, *β* = 0.20. To compensate for a 20% loss to follow-up, the sample size was increased to 44 participants in each group.

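### The test-selection rule names the wrong check and the wrong remedy for unequal variances, and does not say whether it governs the outcomes

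*Protocol article*

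**What the plan says.** Section 2.8 (Statistical analyses) of the protocol article has three linked statements.

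- On checking assumptions: "The Shapiro–Wilk test and box plots will be used to assess the homogeneity of the quantitative variables".
- On the default test, continuous variables "will be performed by Student’s *t*-test at baseline".
- On the alternative: "The Mann–Whitney U test will be selected if the variance was not homogeneous between two groups".

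The section sets the significance level ("a two-sided *p*-value less than 0.05 was considered significant") and gives no other between-group test. Section 2.4 (Estimation of sample size) frames the primary comparison as acupuncture v sham on NIHSS after treatment. It sizes that comparison on means and SDs: NIHSS scores "between the two groups were 6.2 ± 2.1 and 4.9 ± 1.8, respectively, after the treatment".

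**The concern.** Two assumptions seem to have been interchanged. Non-normality is the usual reason for moving to a rank test, and Shapiro–Wilk is the usual check for it. Here Shapiro–Wilk is attached to homogeneity, and unequal variance is what triggers the rank test. No test of equal variances is named. Box plots show spread, but no criterion for acting on them is given.

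The remedy does not fit the problem either. Mann–Whitney addresses whether a value from one arm tends to exceed a value from the other. When the spreads differ, that is not the same question as whether the means are equal, and the test gives no estimate of the 1.3-point difference on which the trial was sized.

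The scope is also unclear. The t-test sentence applies at baseline, while the Mann–Whitney sentence carries no such limit. If the pair governs the outcomes, the observed variances decide which quantity is tested.

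**Working it through.** **The plan's own figure.** Inputs from section 2.4: means 6.2 and 4.9, SDs 2.1 and 1.8, one-sided α = 0.025, β = 0.20.

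- Difference = 6.2 − 4.9 = 1.3. SD ratio = 2.1/1.8 = 1.17.
- Pooled variance = (2.1² + 1.8²)/2 = (4.41 + 3.24)/2 = 3.825, so pooled SD = 1.956.
- n per arm = 2 × (1.960 + 0.842)² × 3.825 / 1.3² = 2 × 7.85 × 3.825 / 1.69 ≈ 35.5, rounded up to 36.

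This reproduces the stated 36, which is therefore a calculation for a comparison of means.

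**Does Shapiro–Wilk detect unequal variance?** No. Its statistic does not change when a sample is rescaled. In simulated normal samples of 44 it rejected in 4.4% at SD 1 and 4.6% at SD 3.

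**What does the rule do to the error rate?** Each scenario has 20,000 simulated trials with equal true means, tested two-sided at 0.05. The protocol names no variance test, so the rule was run as Mann–Whitney if a variance test gives p < 0.05 and Student's t otherwise. The range shown covers a Brown–Forsythe and an F trigger. Arms are 36 v 36 unless stated. The simulation standard error at 5% is √(0.05 × 0.95/20,000) = 0.15 percentage points.

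| Scenario | Student t | Welch | Mann–Whitney always | The rule |
|---|---|---|---|---|
| Normal, SD 2.1 v 1.8 (plan) | 5.2% | 5.2% | 5.0% | 5.2–5.3% |
| Gamma shape 4, SD 2.1 v 1.8 | 4.9% | 4.9% | 5.4% | 4.3–4.4% |
| Normal, SD ratio 2 | 5.0% | 4.9% | 5.6% | 5.5–5.6% |
| Gamma shape 4, ratio 1.5 | 5.2% | 5.2% | 7.4% | 4.8–6.2% |
| Gamma shape 4, ratio 2 | 5.4% | 5.3% | 10.6% | 9.0–10.4% |
| Gamma shape 4, ratio 3 | 5.8% | 5.5% | 14.6% | 14.5–14.6% |
| Exponential, ratio 2 | 5.7% | 5.6% | 29.8% | 14.5–26.0% |
| Normal, ratio 2, 30 v 44, larger SD in smaller arm | 8.2% | 5.1% | 7.6% | 7.6% |
| Normal, ratio 2, 44 v 30, larger SD in larger arm | 3.1% | 5.2% | 4.4% | 4.4% |

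A second skewed set used gamma scores with mean 5.5 and a Brown–Forsythe trigger. The rule rejected in about 6% (SD 1.8 v 3.0, ratio 1.67) and about 11% (SD 2 v 4, ratio 2).

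- With equal arms Student's t alone holds its level, so the switch itself creates the inflation.
- With unequal arms Student's t fails too. The rule's fault there is that it does not repair the problem, whereas Welch does.
- At the planning SDs with normal data, a Brown–Forsythe trigger would change the test in 11.9% of trials and an F trigger in about 15%, with no harm to the error rate.

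**Power at the planning inputs, 36 per arm, simulated:** Student t 79.0%, Welch 79.0%, Mann–Whitney 76.6%.

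**The case against.** The strongest reply concerns reach. The Mann–Whitney sentence directly follows one confined to baseline and can be read as its fallback. On that reading no outcome analysis is affected. An analysis plan may also exist that fixes the primary model. This stands in part: the text does not settle the scope, so the consequence for the primary outcome is conditional. The rule remains technically wrong on either reading.

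The second reply concerns size. A reader might infer that the primary test has an inflated error rate as planned, citing the differing planning SDs, or rejection rates such as 9.2% (SD 1.8 v 3.0) and 17.1% (SD 2 v 4) for skewed scores. The document does not support this. Its own SDs give a nominal rate. Those two figures describe Mann–Whitney applied in every trial, not the conditional rule, and they need skewness plus SD ratios of 1.67 and 2 against a planned 1.17. With normal data and equal arms, a ratio of 2 gives only 5.5% to 5.6%.

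The third reply concerns which null hypothesis is meant. If treatment affects no one, the arms share one distribution and Mann–Whitney is valid. Equal means with unequal SDs is a different state, in which treatment has altered the distribution. This is correct: the excess rejections are errors only for the equal-means null. That null still matters here, because the sample size rests on a difference in means.

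**Conclusion.** The rule is wrong as written on two counts: a normality test is assigned to homogeneity, and a rank test is offered as the answer to unequal variances. Its scope also needs stating. This should be fixed. It does not show that the primary analysis is invalid.

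At the planning SDs with equal arms the rejection rate stays nominal (4.3% to 5.3% at 36 per arm). It rises to about 6% to 11% under assumed skewness with SD ratios of 1.7 to 2. More extreme shapes or ratios give more, as the table shows. It rises to about 7% to 8% under the assumed 30 v 44 retention. That means losing 14 of 44 (32%) in one arm and none in the other, or 14/88 = 16% overall, so it is a demanding case even with the 20% loss the protocol allows for. The document supplies neither the skewness nor the larger SD ratios.

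Confidence is high that the wording is wrong and moderate on its consequences.

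**What to change.** 1. Use Shapiro–Wilk and box plots only to describe distributions, for example to choose between mean with SD and median with quartiles.
2. Delete the variance-triggered switch to Mann–Whitney.
3. Prespecify one primary comparison, acupuncture v sham, of mean NIHSS after treatment or of the change named in the abstract, with a 95% confidence interval. Preferably use a linear model adjusted for the baseline NIHSS already collected, with robust standard errors. With that adjustment the treatment estimate is the same for the post-treatment score and for the change. If no adjustment is wanted, use Welch's test. Choose one now, whatever later checks show.
4. Keep Mann–Whitney as a labelled sensitivity analysis.
5. State whether any remaining test rule covers baseline variables, outcomes or both, and reconcile it with the analysis plan if there is one.

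The cost is a few sentences, settled before unblinding. No extra data are needed, the sample size is unchanged, and power at the planning inputs is not reduced (about 79% for both Student's t and Welch at 36 per arm).

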### Study design

2.1

This is a multicenter, prospective, single-blind, randomized controlled trial that will be conducted in four centers in China. The trial design was approved by the Institutional Review Board of the First Teaching Hospital of Tianjin University of Traditional Chinese Medicine (Tianjin, China) and registered at www.chictr.org.cn (ChiCTR2300079204) in December 2023. This study will be conducted in accordance with the latest version of the Declaration of Helsinki, the Consolidated Standards of Reporting Trials (Schulz et al., 2010), and the Standards for Reporting Interventions in Controlled Trials of Acupuncture guidelines (Macpherson et al., 2010) in trial designing and reporting.

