### Randomization and blinding

2.3

The eligible participants will be enrolled and divided randomly in the acupuncture group (received acupuncture), the control group (received no acupuncture), or the sham acupuncture group (received sham acupuncture) at a ratio of 1:1:1 (*n* = 132) using a computer-generated randomization method. Random numbers were put into an opaque envelope and sealed, and the corresponding serial numbers were affixed to the surface of the envelope for random grouping and concealing. The envelopes were opened according to the order in which the subjects were enrolled for grouping and treatment. The patients will be informed whether they will receive acupuncture treatment or not.

The participants in the acupuncture group and sham acupuncture group will be blinded, while those in the control group will not be. Due to the particularity of acupuncture treatment, it is impossible to blind the acupuncturists in this study. All study personnel including the outcome assessors and data analysts will be blinded to the treatment allocation.

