### Interventions

2.6

All groups will receive the basic treatment of ACI according to the Chinese guidelines for the diagnosis and treatment of acute ischemic stroke 2018, including monitoring and controlling for high blood pressure, sugar metabolic disorder, high cholesterol, and risk factors such as diabetes. The acupuncture and sham acupuncture groups will also receive an additional 30 min of acupuncture therapy as bedside treatment by three acupuncturists who had been trained for at least 3 years and have a master’s degree with more than 5 years of clinical experience, 6 days per week for 2 weeks (12 sessions in total).

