### Outcomes and assessment procedures

2.7

Three independent research assistants will take charge of their data from baseline to 2 weeks and 3 months of follow-up and for evaluating their outcomes.

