#### Primary outcomes

2.7.1

The primary outcome we chose in this study is the NIHSS score that will be measured before and after treatment to evaluate the neurological deficit. There are 15 items in the scale including consciousness, best gaze, motor arm, facia palsy, motor leg, limb ataxia, sensation ability, dysphagia, and neglect. The score of each item scores range from 0 to 4, and the total scores range from 0 to 42. A higher score indicate a more severe neurological deficit.

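### Four hospitals, but the only tests named cannot take a hospital term: if they are used for NIHSS, a little precision may be lost; validity is not affected.

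*Protocol article*

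**What the plan says.** Section 2.1 describes a "randomized controlled trial that will be conducted in four centers in China", and section 2.2 lists the four hospitals. Section 2.3 gives 1:1:1 computer-generated allocation in sealed numbered envelopes: "The envelopes were opened according to the order in which the subjects were enrolled for grouping and treatment". It does not mention stratification or blocking by hospital, or whether each hospital holds its own series.

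On the endpoint, section 2.7.1 says: "The primary outcome we chose in this study is the NIHSS score that will be measured before and after treatment". The abstract describes it as the change in NIHSS. Section 2.4 sizes acupuncture against sham after treatment: "Sample size calculations were performed for a simple comparison of the two groups".

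Section 2.8 assigns Student's t-test to continuous variables in a sentence that ends by referring to baseline. It then adds: "The Mann–Whitney U test will be selected if the variance was not homogeneous between two groups". The section closes with intention-to-treat and a two-sided 5% level. It names no regression model and does not explicitly tie any test to post-treatment NIHSS.

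On staffing, section 2.6 has "additional 30 min of acupuncture therapy as bedside treatment by three acupuncturists", and section 2.7 has "Three independent research assistants will take charge of their data from baseline to 2 weeks and 3 months of follow-up". Neither says whether these people are attached to particular hospitals.

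**The concern.** Case mix and basic care can differ between four hospitals, and bedside needling is necessarily delivered on site. A pooled two-sample test treats all patients as one sample, so two things stay in its error: variation between hospital means, and the noise from arms falling unevenly across hospitals by chance. Hospital is known before randomisation, so a term for it cannot bias the arm contrast and needs no new data.

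What is at stake is the precision of the acupuncture v sham difference, for which the plan targets 1.3 NIHSS points. If the envelopes were in fact balanced within hospital, the pooled test would also ignore that balance. Its p-values would then be somewhat too large and its intervals somewhat too wide.

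**Working it through.** **Inputs from section 2.4.** Post-treatment NIHSS 6.2 ± 2.1 and 4.9 ± 1.8; one-sided α = 0.025 (the same critical value as two-sided 0.05); power 80%; 36 per group, raised to 44. The ICC is not given, so I assume a range of 0 to 0.20.

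**The plan's own figure.** Difference = 6.2 − 4.9 = 1.3. Pooled SD = √((2.1² + 1.8²)/2) = 1.956. Then n = 2 × (1.956 × (1.960 + 0.842)/1.3)² = 35.53, so 36 per group, as stated. Power at 36 is 80.5% by the normal formula and 79.4% by the noncentral t. The stated 44 matches 36 × 1.2 = 43.2 rounded up.

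**Idealised gain.** Take 1.956 as the total SD and multiply the residual variance by (1 − ICC). Power at 36 per arm with a hospital term (normal formula) becomes 82.5%, 84.4% and 88.4% at ICC 0.05, 0.10 and 0.20, against 80.5% without. This overstates the gain because it ignores the three degrees of freedom spent and the chance imbalance of arms across hospitals.

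**Simulated gain.** The settings were four equal hospitals, 36 per arm, allocation not stratified, two-sided 5% and 6,000 runs per setting. The Monte Carlo standard error of a power near 80% is √(0.8 × 0.2/6000), about 0.5 points.

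| ICC | t-test | With hospital term | Gain (points) |
|---|---|---|---|
| 0 | 79.1% | 77.3% | −1.8 |
| 0.05 | 80.1% | 79.6% | −0.5 |
| 0.10 | 80.1% | 81.4% | +1.3 |
| 0.20 | 81.6% | 86.3% | +4.7 |

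Repeat simulations of the same design gave gains of −0.2 to 0.0 points at 0.05, 1.2 to 1.8 at 0.10 and 4.5 to 4.7 at 0.20. The t-test's power rises slightly with ICC because four sampled hospitals show on average only three quarters of the between-hospital variance. At ICC 0.20 the realised total variance averages 1 − 0.20/4 = 0.95 of nominal.

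**False-positive rate of the pooled t-test.**
- Unstratified: 0.050 to 0.056 over ICC 0 to 0.20, which is near the nominal 5%.
- Balanced within hospital: 0.046, 0.045 and 0.034 at ICC 0.05, 0.10 and 0.20. A repeat gave 0.044, 0.037 and 0.036. This is mildly conservative, at about 3.5% to 4.5%.

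**Sensitivity to the SD.** The article does not say whether the borrowed SD already contains hospital variation. If 1.956 is a within-hospital SD, the total SD is 1.956/√(1 − ICC). Unadjusted power at 36 by the normal formula is then 78.5%, 76.3% and 71.3% at ICC 0.05, 0.10 and 0.20.

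**The case against.** The strongest reply is that section 2.8 assigns no test to the NIHSS outcome. The t-test is worded for baseline, the Mann–Whitney sentence can be read as its fallback, and the simple comparison in section 2.4 describes the sample-size calculation. The primary model could sit in an analysis plan that is not shown. This stands to the extent that applying these tests to NIHSS is an inference, so the point is conditional. It does not remove the point. The only tests in print are unadjusted two-sample tests, and they sit beside outcome-analysis rules (intention-to-treat, two-sided 5%) and an unadjusted sizing of the primary contrast.

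A second reply is that one NIHSS entry range (section 2.2.2) and one treatment guideline (section 2.6) limit hospital differences, so an ICC of 0.20 may be too high. That is fair: nothing in the article supports a particular value, and at 0.05 or below the term gains nothing.

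A third reply is that a change score already removes stable hospital differences in baseline severity. In part it does, which is why the model should also carry baseline NIHSS. With baseline as a covariate, the arm difference is the same for the change and for the final score.

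Three stronger readings are tempting but not supported:
- **Rating is local, so a hospital term removes rater variation.** Section 2.7 gives three assistants for four hospitals and does not say where they work. Raters need not map onto hospitals.
- **The trial has no reserve.** Section 2.4 raises 36 to 44 per group. Noncentral t power is 84% at 40 and 87% at 44. Only if the full 20% is lost does 44 × 0.8 = 35.2 bring it back to about 36, and NIHSS is measured around a two-week course, not at three months.
- **The pooled test is invalid.** Its size is near 5% without stratification. The conservative result needs balance within hospital, which section 2.3 does not state.

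**Conclusion.** The point holds as a small efficiency improvement. If the named tests are used for post-treatment NIHSS, hospital variation and chance imbalance of arms across hospitals stay in the error. Under the allocation as described there is no bias and no inflation of type I error.

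The power lost by leaving hospital out is about none at an ICC of 0.05 or below, 1 to 2 points at 0.10 and about 5 points at 0.20. With no hospital differences, the term costs up to about 2 points. These figures assume 36 analysed per arm, equal hospitals, the plan's means and SDs with 1.956 as the total SD, and an ICC that is my assumption. They do not include any gain from baseline adjustment, because the article gives no correlation between baseline and post-treatment NIHSS.

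**What to change.** State in section 2.8 that the acupuncture v sham comparison of post-treatment NIHSS, and the corresponding comparisons of FMA and BI, use a linear model with arm, hospital (four-level fixed effect) and the baseline value of the same scale. Report the adjusted mean difference with its 95% CI, and keep the unadjusted two-sample test as a sensitivity analysis. The model is suitable whether or not the envelopes were issued by hospital.

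The cost is one or two sentences and three degrees of freedom for hospital, plus one for baseline, with a slight loss of power if hospitals do not differ. No new data are needed, since hospital is known and the baseline scales are already collected. The choice should be fixed before outcome data are seen, because a covariate added later is open to challenge.
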